### 2.8. Timing of EARS Administration

The primary EARS assessment will be performed four weeks after the prescription of the home exercise programme. This timing was selected to provide sufficient exposure to the prescribed programme while limiting excessive recall burden. If a participant has not had at least two weeks of opportunity to perform the prescribed home programme because of illness, interruption of care, or other reasons, EARS administration will be postponed until this minimum exposure has occurred, and the delay will be recorded.

### 2.9. Sample-Size Rationale

The sample-size rationale is based on the precision of the descriptive estimate of the mean EARS score rather than on hypothesis testing. Assuming a conservative standard deviation of approximately 6 points for the EARS total score and a desired 95% confidence interval half-width of approximately 1.5 points, at least 62 analyzable participants would be required. To account for incomplete questionnaires, withdrawal, or loss to follow-up, the target recruitment sample will be approximately 75 participants. Exploratory association analyses will be interpreted cautiously and will not be considered confirmatory.

### 2.10. Ethical and Data Protection Considerations

The protocol will be submitted to the corresponding research ethics committee before any data collection begins. No participant recruitment or research data collection will take place before the relevant ethical approval has been obtained. Participation will be voluntary, and patients will receive written and verbal information about the aim of the study, the nature of their participation, the type of data collected, and their right to withdraw without consequences for their clinical care.

Only data necessary for the declared research objective will be collected. Personal identifying data will be separated from the analytical database. Each participant will be assigned a unique alphanumeric code. Access to identifiable data will be restricted to authorised members of the research team. Results will be reported in aggregate form, preventing individual participant identification.

## 3. Materials and Equipment

### 3.1. Participant Information and Consent Document

Draft templates for the participant information sheet, informed consent form, personal data processing consent form, and consent withdrawal form will be provided as Supplementary Material. These documents are draft materials and will require approval by the corresponding Ethics Committee before use in participants.

### 3.2. Clinical Data Collection Sheet

A structured clinical data collection sheet will be used to record the mandatory core variables and optional contextual variables. The form will be linked to the participant code rather than directly to identifiable information.

### 3.3. Home Exercise Programme Record

A structured home exercise programme record will be used to document the prescribed exercises, frequency, dose, duration, progression, and instruction format. This record is essential for interpreting EARS responses because adherence depends on the characteristics of the prescription.

### 3.4. Data Storage System

Data will be stored in a secure digital file or an encrypted database. If paper questionnaires are used, they will be kept in a locked cabinet in a restricted-access area. Digital files will be password-protected and stored according to institutional data protection policies.

### 3.5. Statistical Software

Data will be analysed using IBM SPSS Statistics, version 29.0 (IBM Corp., Armonk, NY, USA), R, or an equivalent statistical package available at the time of analysis. The software and version used will be reported in any subsequent empirical publication.

## 4. Detailed Procedure

### 4.1. Identification of Eligible Participants

Patients attending physiotherapy after WAD or non-surgical post-traumatic neck pain will be screened according to the eligibility criteria by a member of the research or clinical team familiar with the protocol.

### 4.2. Participant Information and Consent

Eligible patients will receive the participant information sheet. The researcher or clinician will explain the study in clear language, clarify that participation is voluntary, and indicate that refusal to participate will not affect clinical care. Patients who agree to participate will sign the informed consent form before any study-specific data are collected.

### 4.3. Participant Code Assignment

After consent, each participant will be assigned a unique alphanumeric code. This code will be used on questionnaires and data collection forms. The correspondence between participant identity and code will be stored separately from the analytical database.

### 4.4. Baseline Clinical Data Collection

Baseline data will be collected using the structured clinical data sheet. The mandatory dataset will include sociodemographic variables, diagnostic category, time since injury, mechanism of injury, pain intensity, and rehabilitation-related variables.

### 4.5. Recording of the Prescribed Home Exercise Programme

The prescribed home exercise programme will be recorded before EARS administration using the structured programme record. If the prescription is insufficiently defined, the clinician will complete the prescription details before the participant is considered eligible for adherence assessment.

### 4.6. EARS Administration

The EARS will be administered four weeks after the prescription of the home exercise programme. Participants should complete the questionnaire independently whenever possible. To mitigate social desirability bias, participants will be informed that there are no right or wrong answers, that responses will not affect their clinical care, and that honest reporting is needed to understand the feasibility of home exercise prescription. The treating clinician should not suggest responses or frame adherence as a desirable behaviour during completion.

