Home exercise adherence is particularly challenging because the programme is performed outside the supervised clinical environment and depends on self-efficacy, motivation, social support, symptom behaviour, contextual barriers, and the feasibility of integrating exercise into daily life [13,14,15,16,17,18,19]. In cervical trauma rehabilitation, adherence assessment is especially relevant because symptoms may fluctuate over time, psychological factors may influence recovery, and home exercise is often used to promote self-management and progressive return to function. Without standardised adherence assessment, it is difficult to determine whether limited improvement reflects treatment ineffectiveness or insufficient exposure to the prescribed programme.

Measuring adherence to home exercise remains a methodological problem. Systematic reviews have shown marked heterogeneity in the methods used to assess adherence in home-based rehabilitation, with frequent reliance on diaries, self-reported questionnaires, and ad hoc measures [20,21,22]. This lack of standardisation limits comparability between studies and reduces the interpretability of exercise-based rehabilitation outcomes.

The Exercise Adherence Rating Scale (EARS) was developed to provide a brief, exercise-specific, patient-reported measure of adherence to prescribed home exercise [23]. The main adherence section consists of six items scored on a Likert-type scale, with a total score ranging from 0 to 24, where higher scores indicate greater adherence [23,24]. The original development study reported a one-factor structure explaining 71% of the variance in exercise adherence and acceptable psychometric properties [23]. Since then, the EARS has been adapted and evaluated in several languages and musculoskeletal populations, including Brazilian Portuguese, Nepali, Japanese, Swedish, Mexican Spanish and Persian versions [24,25,26,27,28,29].

To the authors’ knowledge, no previous protocol has specifically standardised the use of the EARS to assess adherence to prescribed home exercise in adults undergoing rehabilitation after WAD or non-surgical post-traumatic neck pain. This does not imply that the EARS has been psychometrically validated for this population. Rather, it identifies the need for a reproducible implementation protocol that can support consistent adherence assessment and inform future validation studies.

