### 2.6. Protocol Variables

#### 2.6.1. Primary Variable

The primary outcome will be adherence to prescribed home exercise, assessed using the total score of the six-item EARS adherence section four weeks after prescription of the home exercise programme [23]. The EARS total score will be analysed as a continuous variable. No validated cut-off for low or high adherence exists for WADs or non-surgical post-traumatic neck pain; therefore, no diagnostic classification based on EARS cut-off values will be used. Any exploratory categorisation, such as tertiles or sample-based percentiles, will be clearly labelled as exploratory and not clinically validated.

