### 4.7. Missing-Data Management

Before storing the questionnaire, the researcher will check whether all EARS items have been completed. If any item is missing, the participant may be asked to complete it if still present and willing to do so. If the EARS total score cannot be calculated according to scoring recommendations, the participant will be excluded from the primary EARS analysis but retained in descriptive missing-data reporting.

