### 4.10. Critical Points and Methodological Warnings

The following points are critical for reproducibility:The home exercise programme must be clearly documented before adherence is interpreted.The primary EARS administration time point must be four weeks after prescription or after a recorded minimum exposure period.Participants must complete the questionnaire without clinician influence.Instructions must emphasise that honest responses are needed and that answers will not affect clinical care.The linguistic version of the questionnaire must be appropriate for the target population.Data must be anonymised before analysis.The procedure for managing missing data must be predefined.

Potential sources of bias include recall bias, social desirability, variability in prescribed exercise programmes, and the inability of self-report measures to assess technical quality of exercise execution [20,21,22,23,24,27]. The four-week timing, neutral administration instructions, independent completion, standardised prescription recording, and missing-data procedures are intended to reduce these risks, although they cannot eliminate them.

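### Section 4.10 requires EARS completion free of clinician influence, but the procedure in section 4.6 does not exclude the treating clinician, and the listed variables do not record how the form was completed

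*Protocol article*

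**What the plan says.** The primary outcome is home exercise adherence, "assessed using the total score of the six-item EARS adherence section four weeks after prescription of the home exercise programme" (section 2.6.1). The Introduction describes the scale as having six items, "with a total score ranging from 0 to 24, where higher scores indicate greater adherence".

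Three places govern how the form is completed:

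- **Section 4.10**, among the points called critical for reproducibility: "Participants must complete the questionnaire without clinician influence".
- **Section 4.6**, the operating procedure: "Participants should complete the questionnaire independently whenever possible", and "The treating clinician should not suggest responses or frame adherence as a desirable behaviour during completion". The same section gives participants neutral instructions: no answer is right or wrong, care will not be affected, and honesty is needed.
- **Section 4.7**: "Before storing the questionnaire, the researcher will check whether all EARS items have been completed". It continues: "If any item is missing, the participant may be asked to complete it if still present and willing to do so".

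Forms carry a participant code (section 4.3). Section 4.10 names social desirability as a source of bias, counts independent completion among the measures that reduce it, and accepts that the measures cannot remove it altogether.

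**The concern.** The requirement in section 4.10 is absolute, while the procedure meant to deliver it is conditional. A site could follow section 4.6 to the letter with the prescribing therapist in the room, handing over the form or helping with it, provided the therapist neither prompts answers nor presents adherence as desirable. Another site could have the form completed in private. Section 2.2 foresees collaborating centres, so such variation is realistic in a study whose stated purpose is standardised administration.

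The score measures whether patients did what their therapist asked. Being observed by that therapist, or expecting the therapist to read the answers, is a natural route for social desirability. Such bias would probably raise the score, and recruiting more participants would not remove it. If the mode of completion is not recorded, nobody can later see whether it mattered.

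**Working it through.** **1. Requirement against procedure**

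| Question | Section 4.10 | Section 4.6 |
|---|---|---|
| Force | mandatory | advisory |
| Independent completion | counted as a bias-reducing measure | asked for only where it can be managed |
| Treating clinician | no influence allowed | must not prompt or frame; absence not required |
| Who hands out and collects | not stated | not stated |
| When help is needed | not stated | not stated |

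The sentence restraining the treating clinician at completion is needed only if that clinician might be there. The text therefore leaves presence open without expressly granting it.

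**2. Can the mode be examined later?** Section 2.6.2 lists the mandatory variables: demographics, diagnosis, time since injury, mechanism, pain, supervised sessions, programme characteristics, EARS total and item missingness, and barriers. Section 2.6.3 adds medication, comorbidities and digital self-monitoring. Neither list includes whether completion was alone or assisted, or who helped. Section 2.5 has sensory and communication adaptations documented, but as part of the exercise programme record, not of EARS completion.

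**3. The plan's own precision figure.** Section 2.9 gives SD 6, half-width 1.5 and 95% confidence.

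n = (1.96 × 6 / 1.5)² = 7.84² ≈ 61.5, rounded up to 62. This reproduces the plan and is not in dispute.

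SE of the mean = 6 / √62 = 0.76. Half-width at n = 62 = 1.96 × 0.762 = 1.49.

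**4. Illustration of what a bias would do.** The document gives neither the share of forms affected nor the size of any shift, so both are assumptions. With share f and shift d per affected form, the mean moves by b = f × d. Holding the SD at 6, coverage of the nominal 95% interval is Φ(1.96 − b/SE) − Φ(−1.96 − b/SE).

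| f | d (points) | b (points) | Coverage |
|---|---|---|---|
| 0.10 | 1 | 0.10 | 94.8% |
| 0.10 | 3 | 0.30 | 93.2% |
| 0.25 | 1 | 0.25 | 93.8% |
| 0.25 | 3 | 0.75 | 83.4% |
| 0.50 | 1 | 0.50 | 89.9% |
| 0.50 | 3 | 1.50 | 49.7% |

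The range runs from negligible to serious. It shows only that a shift of a point or so in the mean would matter against the precision planned; it does not estimate what will happen.

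**The case against.** The strongest reply is that sections 4.6 and 4.10 do not conflict. One forbids influence and the other concerns independence, and neither presence nor help is the same as influence. Leaving room for people who need assistance is sensible. The protocol also gives neutral instructions, codes the forms and openly admits residual bias. Much of the remaining detail could sit in a manual behind a condensed article.

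Part of this stands. The sections differ in strictness and do not flatly contradict each other, and the safeguards are real. But none of them settles who is in the room or who sees the answers. Participants are told that care is unaffected, not that their therapist will not read the form, and a code does not hide a form from a therapist who collects it. Standardised administration is what this article sets out to specify, so the gap is not merely an operational detail.

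Four stronger readings are tempting and not supported:

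- *The plan permits the treating clinician to be present.* It does not say so; it fails to exclude it.
- *Section 4.7 has answers reviewed.* It describes a check that items are filled in, by the researcher, and does not conflict with section 4.10.
- *The therapist may hand out and read the form because roles overlap.* The shared roles appear in section 4.1 for screening and in section 4.2 for consent ("The researcher or clinician will explain the study in clear language"). Nothing extends them to EARS administration, although nothing separates them there either.
- *The mean will be inflated by a known amount.* No figure in the document supports one.

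**Conclusion.** The point holds as a gap between a strict requirement and a looser procedure. Section 4.6 does not secure what section 4.10 demands, and the listed variables would not show afterwards how each form was completed. The consequence is an avoidable bias in the primary estimate. An upward direction is plausible because higher scores mean more adherence and the score reports compliance with the clinician's own prescription, but the document does not demonstrate that direction. The size cannot be derived, and the figures above rest on assumed shares and shifts. The planned sample size is unaffected. The procedure should be tightened before recruitment, because the mode of completion cannot reliably be recovered later.

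**What to change.** In section 4.6, state that the treating clinician is not present at completion, does not assist with or collect the EARS, and does not see individual answers. Tell participants this together with the existing neutral instructions. Where no other team member is available, use a sealed coded envelope or an electronic link. Any help comes from someone other than the treating clinician.

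Keep the completeness check in section 4.7, because a form that cannot be scored drops out of the primary analysis. Have it done by a researcher who is not the treating clinician, or by a required-item prompt in an electronic form.

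Add the mode of completion to section 2.6.2 (alone or assisted, by what role, paper or electronic) and report EARS by mode descriptively.

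The cost is a few sentences, an extra entry on the data sheet, envelopes or a link, slightly more logistics at small sites, and possibly a few more missing items.

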### 4.7. Missing-Data Management

Before storing the questionnaire, the researcher will check whether all EARS items have been completed. If any item is missing, the participant may be asked to complete it if still present and willing to do so. If the EARS total score cannot be calculated according to scoring recommendations, the participant will be excluded from the primary EARS analysis but retained in descriptive missing-data reporting.

### 4.8. Data Coding and Anonymisation

Questionnaire scores and clinical variables will be entered into the database using only the participant code. Identifiable information will not be included in the analysis file. Data entry will be reviewed to detect possible transcription errors.

### 4.9. Statistical Analysis

Descriptive statistics will be used to summarise participant characteristics, home exercise prescription characteristics, and EARS scores. Continuous variables will be inspected using histograms, Q-Q plots, and the Shapiro–Wilk test. Normally distributed quantitative variables will be expressed as mean and standard deviation; non-normally distributed variables will be expressed as median and interquartile range. Categorical variables will be expressed as frequencies and percentages.

The primary analysis will describe the EARS total score as a continuous variable with 95% confidence intervals when appropriate. Item-level missingness, completion rate, and time required to complete the questionnaire will be reported as feasibility indicators. Because no validated cut-off for low adherence exists in this population, no confirmatory dichotomisation of EARS scores will be performed.

Exploratory associations between EARS total score and continuous variables such as pain intensity, time since injury, number of supervised sessions, and prescribed home exercise duration will be examined using Pearson or Spearman correlation coefficients, depending on distributional assumptions. Differences in EARS scores across categorical variables such as sex, diagnostic category, time-since-injury category, or instruction format will be explored using t-tests, Mann–Whitney U tests, analysis of variance, or Kruskal–Wallis tests as appropriate.

To examine potential contextual factors influencing adherence, an exploratory multivariable linear regression will be conducted to assess associations between the EARS total score and predefined candidate variables. This multivariable analysis will only be performed if the final data structure is appropriate and a minimum participant-to-variable ratio of 10:1 is satisfied to prevent model overfitting. Candidate variables selected a priori based on clinical relevance include age, sex, pain intensity, time since injury, number of supervised sessions, and estimated weekly home exercise burden. If the final sample size of analyzable participants falls below the required 10:1 ratio, or if core regression assumptions (specifically linearity, homoscedasticity, and the absence of multicollinearity) are violated, the multivariable model will be omitted, and analyses will be limited to bivariate correlations. Any multivariable results will be interpreted strictly as exploratory and hypothesis-generating. Regression assumptions will be checked using residual plots and collinearity diagnostics.

Analyses will be interpreted as exploratory. No formal correction for multiple testing will be applied to exploratory analyses; instead, effect sizes, confidence intervals, and consistency of findings will be emphasised. Missing data will be described. The primary analysis will use available complete EARS total scores; no imputation will be performed for the primary descriptive estimate unless prespecified scoring rules support it. If missing data exceed 10% for key variables, sensitivity analyses will be considered.

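### The study is sized on the mean EARS score, but the reporting rule in section 4.9 lets a normality check replace that mean with a median and IQR

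*Protocol article*

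**What the plan says.** Section 2.9 gives one basis for the sample size. It is "based on the precision of the descriptive estimate of the mean EARS score rather than on hypothesis testing". The SD is taken as about 6 points, which the section calls conservative. The precision target and the resulting number are: "a desired 95% confidence interval half-width of approximately 1.5 points, at least 62 analyzable participants would be required". Allowing for losses, "the target recruitment sample will be approximately 75 participants".

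Section 4.9 opens its descriptive paragraph by listing EARS scores together with participant and prescription characteristics. Continuous variables are to be examined with histograms, Q-Q plots and the Shapiro–Wilk test, and no decision threshold is given. The rule is then: "Normally distributed quantitative variables will be expressed as mean and standard deviation; non-normally distributed variables will be expressed as median and interquartile range". The primary outcome is not exempted.

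The next paragraph of 4.9 covers the primary analysis: "The primary analysis will describe the EARS total score as a continuous variable with 95% confidence intervals when appropriate". It does not say whether the interval belongs to a mean or a median. Later in 4.9, the missing-data text speaks only of the primary descriptive estimate, again without naming the statistic. The Introduction describes the scale "with a total score ranging from 0 to 24, where higher scores indicate greater adherence".

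**The concern.** The sample size is justified for one quantity, and the analysis section allows another to be reported in its place. The choice between them depends on an inspection of the data with no stated threshold. EARS is a bounded score, so a skewed sample or one that piles up at an end of the scale is possible. Section 4.10 itself lists social desirability as a bias that its measures cannot eliminate, and over-reporting would push scores upwards.

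This concerns the study's only primary outcome and only sample-size basis. If the switch is made, the main question (what is the level of adherence?) is answered by a median and an IQR. An IQR describes spread between patients and says nothing about the precision of the estimate. The half-width of 1.5 points would not apply. The Introduction presents advance publication of the protocol as protection against selective outcome reporting, and a primary statistic chosen after looking at the data weakens that protection.

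**Working it through.** **1. Reproduce the plan's figure.** Inputs from section 2.9: SD 6, half-width 1.5, 95% confidence.

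n = (1.96 × 6 / 1.5)² = 61.46, rounded up to 62. The figure reproduces, and it is a formula for a mean. At n = 62 the half-width is 1.96 × 6 / √62 = 1.49 with the normal quantile and 1.52 with the t quantile on 61 degrees of freedom. Both agree with the stated 1.5.

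**2. Precision of a median at the same n.** For a normal score, the large-sample standard error of the median is 1.2533 times that of the mean.

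- At n = 62: 1.2533 × 1.493 = 1.87 points.
- For a half-width of 1.5: 1.2533² × 61.46 = 96.5, so 97 participants, which is more than the recruitment target of 75.
- With all 75 recruited and no losses: 1.2533 × 1.96 × 6 / √75 = 1.70 points.

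For bounded integer scores with SD 6 and assumed means of 12 to 18, a distribution-free interval (23rd to 40th ordered value of 62) had a simulated average half-width of about 2.1–2.6 points. For the beta shape it was 2.58 at mean 12, 2.51 at mean 16 and 2.29 at mean 18. This interval is somewhat conservative, so not all of the extra width is due to the median itself.

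**3. How often would a normality test reject?** The documents give no expected mean, no shape and no test level, so all three are assumed here. Simulation: n = 62, integer scores on 0–24, Shapiro–Wilk at 0.05, 2000 samples per setting, three shapes (rounded beta, beta-binomial, rounded normal clipped at 0 and 24). For the clipped normal, mean and SD are the values before clipping; at nominal mean 16 and SD 6 they become 15.8 and 5.52. The cells give the range of rejection rates over the three shapes.

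| Assumed mean | SD 6 | SD 5 | SD 4 |
|---|---|---|---|
| 12 | 8–51% | 6–20% | 9–10% |
| 14 | 18–70% | 7–35% | 9–18% |
| 16 | 64–98% | 28–81% | 10–50% |
| 18 | 97–100% | 87–100% | 51–95% |

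Rejection is the majority outcome for every shape tried once the mean reaches about 16 at SD 6, or about 17 at SD 5. For mid-scale means with SD 4 or 5 it is usually a minority outcome.

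**4. Is normality needed for the interval of the mean?** With beta-shaped scores, SD 6 and n = 62, the t-based 95% interval for the mean covered the true mean in 95.1–95.2% of samples at means 12, 16 and 18, with average half-width 1.52. Over the wider set of assumed settings, coverage was about 93–96%. The planned interval therefore works without normal raw scores.

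**The case against.** The best defence is that the mean/median rule is a general convention for summary tables, while the primary analysis has its own paragraph. Section 2.9 names the mean as the target, section 4.9 promises a confidence interval for a continuous score, and nothing forbids printing a mean beside a median. Section 5 lists the distribution of EARS totals as an output, which invites several summaries. On this reading a mean with its interval is clearly intended. That is plausible, but the text does not secure it: EARS scores are listed under the rule, the primary sentence names no statistic, and the interval is conditional.

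A reader might infer more: that the mean would be displaced in most plausible samples, or never reported. The documents do not support this. They state no expected mean or shape, and the rejection rates above run from about 6% to 100% depending on what is assumed. The protocol calls its SD of 6 conservative, so a smaller SD, with lower rejection rates, is consistent with its own expectation. The rule also uses plots and fixes no threshold, so a Shapiro–Wilk rejection rate is not a switching rate.

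A reader might also infer that a median could not be compared with other EARS studies. That would need to know how those studies report, which the documents do not say, so no weight is put on it.

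Finally, a separate analysis plan may exist. The exact type of interval could be left to it. The rule that decides between mean and median is different, because it is written in this document and conflicts with this document's sample-size basis.

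**Conclusion.** The point holds as an inconsistency between sections 2.9 and 4.9. The study is sized for the mean, and a stated rule can replace the mean with a statistic that has no planned precision. How likely this is cannot be read from the documents. Under the assumed distributions it is likely if scores lie towards one end of the scale, and uncertain or unlikely if they centre near the middle with a smaller spread.

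The loss of precision is moderate: from about 1.5 points to about 1.87 if scores are normal, or about 2.1–2.6 for the bounded shapes tried with SD 6 and means 12 to 18. Heavier piling at the maximum can instead make a median interval narrow. In neither case does the planned 1.5 describe the median.

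This is a should-fix point, not a critical one. The study is a single descriptive cohort with no confirmatory test, the 62 is correct for its stated purpose, and the collected data would still allow the mean and its interval to be computed.

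**What to change.** In section 4.9, exempt the EARS total score from the mean/median rule and name the primary estimate. Suggested wording: *The primary estimate is the mean EARS total score with its two-sided t-based 95% confidence interval, reported whatever the normality check shows; the median and interquartile range are reported in addition.* Delete the qualifier *when appropriate* for the primary outcome. The normality-based rule can stay for the other variables.

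The cost is a sentence or two of wording, to be settled before data collection. The 62 analysable and approximately 75 recruited participants stay as they are, no further data are needed, and a skewed distribution would still be visible from the added median and IQR.
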